## Abstract

**Background:**

Cannabis is the most consumed illegal substance in France. General practitioners (GPs) are the health professionals who are most consulted by adolescents. Brief intervention (BI) is a promising care initiative for the consumption of cannabis, and could be a tool for GPs in caring for adolescents who consume cannabis. The aim of the CANABIC study is to measure the impact of a BI carried out by a GP on the consumption of cannabis by adolescents of 15 to 25 years of age.

**Methods:**

A randomized clustered controlled trial, stratified over three areas (Auvergne, Languedoc-Roussillon, and Rhône - Alpes), comparing an intervention group, which carries out the BI in consultation, and a control group, which ensures routine medical care. The main assessment criterion is the consumption of cannabis by amount of joints per month, at 12 months. The amount necessary to highlight a significant difference between the two groups of 30% of consumption at 12 months is 250 patients (50 GPs, 5 patients per GP; risk α = 5%; power = 90%; intra-cluster correlation coefficient ρ = 0.2; Hawthorne effect = 15%; lost to follow-up rates for GPs = 10% and for patients = 20%). This plan is replicated for the three areas, and therefore a total of 750 patients are expected.

The secondary criteria for judgment are the associated consumption of tobacco and alcohol, the perception of the consequences of consumption, and the driving of a vehicle following consumption.

**Discussion:**

Research about BI for young cannabis users is underway. The aim of the CANABIC study is to validate a BI suited to adolescents who consume cannabis, which may be performed in the general practice. This would provide a tool for their treatment by a GP, which could be widely distributed during initial or further medical training.

**Trial registration:**

CANABIC is a randomized clustered trial (NCT01433692, registered 2011 Sept 12), PHRC funded: Clinical Research Hospital Program (Governmental Fund, Health Ministry). Date first patient randomized: March 2012.

## Background

In Europe, 12.1% of people aged from 15 to 34 state that they have consumed cannabis in the past year, vs. 16.7% in France and 24.1% for the United States [1]. In France, cannabis is the most consumed illegal substance [2]; 39% of 15 to 16-year-olds [3] and 41.5% of 17-year-olds [4] have previously smoked cannabis. This consumption relates mainly to persons below 25 years of age with an average age of experimentation of 15 [2]. Various levels of consumption are described: recent users (used at least once in the previous month), occasional (1 to 9 times per year), repeated (10 uses/year to 10 uses/month), regular (10 to 29 per month), and daily (at least once per day) [1]. In France, in 2011, 24% of young people between 15 and 16 years of age and 25% of 17-year-olds were recent consumers vs. 15% and 25% in 2007 [3,4].

Current data are clear about the risks of cannabis use: social and psychiatric risks, and highway accidents after smoking [5]. There is no consensus over the treatment of adolescents who consume cannabis. In 2008, a review of the literature explored the out-patient strategies used: motivational interviewing (MI) seems to have positive results in terms of the reduction of consumption of cannabis by young people of less than 18 years of age [6]. This was confirmed in 2013; cognitive-behavioural therapies, MI, and family therapy enable a reduction in the consumption of cannabis [7]. MI was described by Miller and Rollnick in the early 1980’s [8], as a method of interaction centred on the patient intended to modify behaviours by working on the ambivalence of the patient, naturally generated by the prospect of change. The period of psychological and physical development of adolescence makes it a target that is particularly suited to this technique. Brief intervention (BI) is a technique for motivational counselling characterized by its short duration. Its criteria of effectiveness are described using the acronym FRAMES [9]: Feedback, Responsibility, Advice, Menu, Empathy, Self-efficacy. In various European countries, trials have shown an effectiveness of BI on the consumption of alcohol [10,11]. A Canadian and an Australian study have shown the acceptability of BI among consumers of cannabis [12,13], and a trend towards a reduction in their consumption of cannabis [12,13]. A trial showed a reduction in the frequency of consumption at 3 months among young consumers who had been given a BI [14]. However, these studies were not undertaken in general medicine, but in facilities specialized in addiction or in school groups. A Swiss study showed good acceptability and feasibility of BI among general practitioners (GPs) and their young patients [15], without demonstrating its effectiveness.

The 2008 report by the World Organization of Family Doctors on mental health [16] stressed that the treatment of addiction in primary healthcare is beneficial to the improvement of the overall health condition of patients and reduces the social and economic costs that are borne by patients and their carers. In France, the structure of primary healthcare is primarily based on GPs, who are the health professionals that are most consulted by adolescents. One in seven patients consulting general medicine is aged between 11 and 20 [17]. Furthermore, for every seven patients, a GP sees one recent consumer during consultation [18]. Recourse to the healthcare system increases alongside increased cannabis consumption [19].

The 2009–2012 European Union Action Plan on drugs [20] and the 2nd French Governmental Plan (2009–2011) [21] of the Inter-ministerial Mission for the Fight Against Drugs and Drug-Addiction prioritised prevention and the development of basic and clinical research. The training of primary healthcare doctors and other healthcare professionals for early identification was also a priority area.

However, a French study in 2011 showed that only 8% of GPs questioned adolescents on their consumption of cannabis [22], indicating that there are difficulties on the part of adolescents but also on the part of GPs in addressing this topic. In 2009, the authors carried out a qualitative survey intended to identify the barriers discouraging GPs from speaking about cannabis with young patients. The majority of the 24 GPs, grouped into three focus groups, did not speak about it because they felt insufficiently trained in the identification and the treatment of cannabis consumers, and did not know how to address the topic. They were even less at ease if they had known the adolescent for a long time. The illegal aspect of the substance was an additional barrier to discussion. They all lamented the trivialisation of consumption but also deemed that it was within the remit of the private life of a young patient.

The authors also undertook a qualitative study focusing on the reluctance of adolescents to discuss their health issues with their GP, and especially their consumption of cannabis [23]. They were ambiguous with their GP, who they perceived to be both moralizing and the person who is responsible for addressing the topic. They were more comfortable speaking about it if they had known the GP for a long time and if they were alone during the consultation.

The authors hypothesize that in France, a BI in general medicine could enable identification of cannabis consumption in adolescents and propose early treatment, intended to reduce their consumption.

The main objective of the CANABIC study is to measure the effect at 12 months of a BI by GPs on cannabis consumption among recent user adolescents of 15 to 25 years of age. The secondary objectives relate to the variations in intermediate cannabis consumption at 3 and 6 months, variation in consumption associated with other methods of consumption (e.g., “bongs”), variations in consumption associated with alcohol and tobacco, the change in the perception of adolescents regarding the effects of their cannabis consumption on their personal, social, and professional lives, and on driving following the consumption of cannabis.

## Methods

The main assessment criterion is the amount of joints consumed per month at the 12^th^ month following the inclusion consultation. In the absence of consensus on the definition of a threshold for dangerous cannabis consumption, it is impossible to refer to a target level of consumption. In the light of epidemiological data (proportions of recent, repeated, regular, and daily users in the age group 15–25 years) [1,2], we considered that cannabis users consumed an average of 15 joints per month. Our working hypothesis is that the intervention will result in a 30% reduction in the stated consumption of cannabis at 12 months (that is to say five joints per month). The Hawthorne effect [24] was taken into account by estimating that adolescents of the control group would reduce their consumption by 15% (i.e., two joints per month).

A difference of 30% between the intervention group (i.e., three joints per month) and the control group appears to be clinically relevant.

Some secondary hypotheses are reported in case report forms (CRFs) at 3, 6, and 12 months by the GP: the change to other methods of cannabis consumption such as consumption by “bong” or “water pipe” and the impact of the change in cannabis use on tobacco and alcohol consumption.

Other secondary hypotheses are collected by a declaratory self-administered questionnaire completed by the patient at the start and end of the study: how it is consumed (alone or with friends, weekday or weekend, joints or bongs), changing perceptions of the danger of consumption for health, and driving after smoking.

### Study design

It is a clustered randomized comparative multicentre trial, stratified by region (Auvergne, Rhône-Alps, Languedoc-Roussillon), conducted by 150 GPs, assigned to an intervention group (IG) or a control group (CG) (Figure 1). The intervention consists of a BI carried out in general medicine. The patients are included during a consultation, regardless of the reason for the consultation, and are monitored over 12 months. Each doctor must include 5 patients, that is to say 750 patients in total; 50 doctors are recruited in the three regions, 25 for the intervention group and 25 for the control group.

**Figure 1 F1:**
[figure not shown]
Global design of the CANABIC study.

In the three regions, all practising GPs are invited to take part in the trial by mail. Doctors with an exclusive specialty (e.g., acupuncture, homeopathy) and doctors who have received specialized training in addiction treatment (e.g., university degree, qualification, university course) cannot take part in the trial.

Six coordinating doctors manage a group in each region. Their role is to make investigators continue inclusions, answer their questions, and link investigators on the ground to the main investigator.

### Intervention versus usual care

#### Usual care

Investigators registered in the control group provide care according to their usual practices.

#### Intervention

The investigators registered in the intervention group conduct an interview according to the BI model, defined as six key stages using the acronym FRAMES [9]:

•Feedback: returning the trial results to the patient.

•Responsibility: empower the patient by letting him establish his program for reducing or stopping consumption.

•Advice: advising moderation.

•Menu: discussing with the patient possible changes to his/her consumption.

•Empathy: treating the patient with kindness.

•Self-efficacy: allow the patient to be in charge of his/her own changes.

It is an interview outline; as this is a pragmatic trial aiming to assess the impact of BI in daily clinical practice, the delivery of the intervention is allowed to vary between health care providers. The health care providers have the flexibility to adapt the BI according to the patients’ needs.

The GPs of the intervention group are trained to carry out the BI during a standard consultation through a training day designed by the authors.

The training course was defined according to three objectives:

•Updating the knowledge of GPs regarding cannabis: levels of consumption, method of consumption, harmful effects, possibility of treatment.

•Removing communication barriers in order to facilitate discussion by returning the summary of results of the two qualitative studies. Emphasis was placed on contradictory beliefs, the expectations of adolescents, and the reluctance of doctors.

•Training GPs in BI (theoretical explanation, exercise in formulation of open-ended questions, practice through role-playing).

### Inclusion and non-inclusion criteria

#### Inclusion criteria

All young persons from 15 to 25 years of age consuming at least one joint per month for at least one year and registered with a social security scheme are eligible for the study (as stated in the law: Code of Public Health. Article L1121_11*).*

#### Non-inclusion criteria

•A patient suffering from psychiatric illness and who requires immediate specific care, at the discretion of the attending doctor.

•A patient suffering from intellectual disabilities, deafness, or who does not have a command of the French language.

•A patient previously treated for withdrawal from cannabis addiction or addiction to another substance.

•Patients who have participated in one of the preliminary qualitative studies.

### Recruitment

In both groups, the investigators identify eligible adolescents who consume cannabis by asking them the following questions: “Do you smoke cannabis? For how long have you smoked it? How much do you smoke?” The volunteer GPs recruit the first five eligible adolescents that they consult, regardless of the reason for their consultation. Participation requires a prior consent, a guarantee of anonymity, and an unconditional right to withdraw.

During this consultation, the investigators of the intervention group conduct an interview using the BI technique with the eligible and voluntary adolescents.

The doctors of the two groups provide the patient with an anonymous self-administered questionnaire to complete during the consultation. This self-administered questionnaire makes it possible to collect additional information such as method and times of consumption, monthly cost of consumption, and a cannabis abuse screening trial (CAST) score. The self-administered questionnaire is used in order to not influence the course of the consultation with adolescents of the control group and reduce the Hawthorne effect.

During the follow-up consultation at 3 and 6 months, the main assessment criterion is specified as well as cigarette and alcohol consumption. The investigators of the intervention group carry out a BI at each consultation. During the final consultation at 12 months, the doctors of the two groups provide another self-administered questionnaire.

If the adolescent does not attend the following consultation, the doctor can contact him/her by phone to make another appointment or at least to obtain the required data. To help investigators, the coordinators send a schedule of the consultations expected for each patient, as well as reminders to the GPs.

### Randomization

The doctor’s surgery is the unit of randomization. Patients of an investigator GP are assigned to the same group as him/her. Investigators from the same doctor’s surgery are randomized within the same group in order to avoid contamination bias. As the study is being carried out in three regions in which behaviours in terms of cannabis consumption and sociodemographic parameters may differ, the randomization is stratified by region and by state and is carried out using Stata, version 12 (StataCorp, College Station, USA). Taking into account the risk of contamination generated by adolescents who discuss the study with their peers while their doctors belong to different groups, collection of the name of the school/college and the class is planned in order to evaluate the possible impact of interpenetration. The same will apply for registration with one or several associations (patients were asked about their membership in a sports or cultural association; data was collected by GP during consultation).

### Statistical considerations

#### Sample size estimation

The calculation of the necessary amount of adolescents was carried out on the basis of a variation in consumption between the randomization groups of the amount of joints at 1 year, based on data from literature relating to the effect of a BI on alcohol consumption [10]. Given that the published data has heterogeneous values in terms of standard deviation associated with the quantity of joints consumed and considering the importance of a possible declarative bias, various simulations were carried out according to the value of this standard deviation (s = 1.5, 2, 3, 4 and 5) for 90% power and 5% two-sided type 1 error taking into account inclusion of five patients per GP, clustering by practice (intra-cluster correlation considered between 0.05 to 0.20 [25,26], a 10% dropout rate of GP and 20% of patients [27]). By considering the results of these simulations, a minimum of 250 patients is required to highlight a relative variation in the reduction in consumption of the amount of joints of 50% between the two groups (30% vs. 15%). This represents 50 investigators (25 in each randomization group). This design is respected in each region for an analysis stratified by region and thus highlights a variation per region. In total, 150 investigators (50 per region) must include 750 patients.

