Any adolescents who consume cannabis are eligible, on the condition that they smoke at least one joint per month. These levels of consumption may appear highly dispersed, but the European School Survey Project on Alcohol and other Drugs and the Survey on Health and Consumption administered during the Defence Preparation Day data described correlations between quantity consumed and certain behaviours (without causal links to date), e.g., runaways, school absenteeism, depression, and acts of violence. The difference in behaviour between occasional and regular consumers is less significant than between occasional consumers and non-consumers [18]. These consumers thus constitute a homogeneous group as regards behaviour. The selection of the 15–25 age bracket appears to be relevant for carrying out a trial on intervention on cannabis consumption. Fifteen years of age is the average age of experimentation with cannabis, and 25 years of age is the apex of consumption [2]. Consumption is quite homogeneous; in the 19–25 age bracket, 14.6% are repeat consumers [2], and in 12–19 year olds, 16.4% are repeat consumers [3].

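### The planning SDs of 1.5 to 5 joints are implausibly small for the eligible population, so the 90% power claimed at 250 patients per region is not supported

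*Protocol article*

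**What the plan says.** All references are to the protocol article.

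- **Sample size estimation.** Published data are said to have "heterogeneous values in terms of standard deviation associated with the quantity of joints consumed". The response is a grid: "various simulations were carried out according to the value of this standard deviation (s = 1.5, 2, 3, 4 and 5". It is run "for 90% power and 5% two-sided type 1 error", with five patients per GP, an ICC of 0.05 to 0.20, and dropout of 10% of GPs and 20% of patients. The conclusion is a minimum of 250 patients for reductions of 30% and 15% in the two groups. The design is then repeated in each of three regions, for 750 in total. The SD that produced 250 is not named.
- **Methods (opening section).** "we considered that cannabis users consumed an average of 15 joints per month". The section rounds the two reductions to five and two joints, and so the difference to three.
- **Inclusion criteria.** Patients qualify by "consuming at least one joint per month for at least one year". There is no upper limit.
- **Background.** The highest use categories are "regular (10 to 29 per month), and daily (at least once per day").
- **Discussion.** "These levels of consumption may appear highly dispersed", a remark that the article then argues against.
- **Statistical analyses.** The mixed model adjusts for the baseline joint count.

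**The concern.** Required sample size grows with the square of the SD, so a sensitivity grid is useful only if it reaches values the population could produce. This one stops at 5 for a count averaging 15. At that value a normal shape would put 95% of patients between about 5 and 25 joints, although the criteria admit patients at one joint a month and daily users at 30 or more.

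The 90% figure is claimed for each region, and the design is tripled so that regional variation can be shown. If regional power is far lower, a non-significant regional result would be read against a power figure that the design may not have.

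**Working it through.** **Inputs.** Two-sided alpha 5%, power 90% (z = 1.960 and 1.2816, sum 3.2415). Mean 15. Difference 2.25 joints (15 × 0.85 = 12.75 against 15 × 0.70 = 10.5) or the rounded 3. Retained fraction 0.9 × 0.8 = 0.72, so n per arm is 250 × 0.72 / 2 = 90, or 270 for 750. Design effect (deff) = 1 + (m − 1) × ICC, with ICC 0.05 to 0.20 and m = 5 (planned) or 4 (roughly retained).

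**Formulas.** Power = Φ(δ / (SD × √(2 × deff / n)) − 1.96). Total N = 4 × 3.2415² × SD² / δ² × deff / 0.72. With baseline correlation r, SD is replaced by SD × √(1 − r²).

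**1. The plan's 250.** At δ = 2.25, ICC 0.2 and m = 5, N is 47, 83, 187, 332 and 519 for SD 1.5, 2, 3, 4 and 5. None is 250. The closest match using the abstract's ICC of 0.2 is δ = 3, SD 5, m = 4: N = 259, and 88.9% power at 250. The match is not unique, because the SD used is not stated.

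**2. Largest SD that keeps 90% power (unadjusted).** Example: δ = 2.25, ICC 0.2, m = 5 gives √(2 × 1.8 / 90) = 0.2 and SD = 2.25 / (3.2415 × 0.2) = 3.47. Over all ICC and m values:

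| Patients | δ = 2.25 | δ = 3 |
|---|---|---|
| 250 | 3.5-4.3 | 4.6-5.8 |
| 750 | 6.0-7.5 | 8.0-10.0 |

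Inside the plan's own grid, SD 5 with δ = 2.25 falls short. At ICC 0.2 and m = 5, power is Φ(2.25 / 1.0 − 1.96) = 61%, and the most favourable cell gives 80%.

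**3. Is SD 5 or less plausible at mean 15?**
- Patients with identical Poisson rates would have SD √15 = 3.9. This is a benchmark, not a lower limit.
- By the one-sided Chebyshev inequality, SD 5 allows at most 25 / (25 + 225) = 10% of patients at 30 or more, and at most 25 / (25 + 100) = 20% at 5 or fewer.
- Counts spread evenly from 1 to 29, with no daily users, have mean 15 and SD √((29² − 1) / 12) = 8.4.
- Illustrative mix: 40% at 5, 40% at 17, 20% at 31. Mean 15, variance 40 + 1.6 + 51.2 = 92.8, SD 9.6.
- Illustrative mix: 50% at 4, 30% at 18, 20% at 38. Mean 15, variance 60.5 + 2.7 + 105.8 = 169, SD 13.

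The even spread and the mixes are assumptions; the documents do not give the enrolled distribution.

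**4. Power (%) under assumed SDs,** as ranges over ICC 0.20 to 0.05 and m = 5 or 4:

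| SD | r | 250, δ 2.25 | 250, δ 3 | 750, δ 2.25 | 750, δ 3 |
|---|---|---|---|---|---|
| 8 | 0 | 29-42 | 47-65 | 68-86 | 90-98 |
| 10 | 0 | 20-29 | 32-47 | 50-68 | 74-90 |
| 15 | 0 | 11-15 | 17-24 | 25-37 | 41-58 |
| 8 | 0.7 | 50-69 | 75-91 | 93-99 | over 99 |
| 10 | 0.7 | 35-50 | 56-75 | 78-93 | 95 to over 99 |
| 13 | 0.7 | 23-33 | 37-52 | 56-75 | 80-94 |

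The correlation of 0.7 is also an assumption.

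**The case against.** **The SDs may be residual, or of change.** The text ties them to the quantity consumed. A residual SD of 5 from a marginal SD of 10 needs r = √(1 − 0.25) = 0.87, which is nowhere claimed. Baseline adjustment is planned, however, and must be credited. It lifts every figure, and at SD 8 with three joints the most favourable cell at 250 just reaches 91%. Repeated measurements may add a little more.

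**The difference may be larger.** The abstract can be read as a 30% difference between groups, or 4.5 joints. The limits for 2.25 joints would then double, to about 6.9-8.7 at 250. But the sample size section specifies 30% against 15%, and the Methods section gives three joints.

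**The range rests on published data,** which are not available here. That stands, and it is why the loss can only be shown as a range.

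Three stronger readings are tempting and are not supported:

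- A reader might infer that SDs of 1.5 to 3 are impossible because they lie below the Poisson value. Self-reported habitual use can be under-dispersed, and the planned model is linear. Implausible is as far as the evidence goes.
- A reader might infer that SD 5 contradicts the stated population. The article gives an eligibility floor and use categories, but no enrolled shares for the Chebyshev limits to contradict. The remark on dispersion is raised in order to be answered. That answer concerns behaviour and age brackets, though, not the spread of joint counts.
- A reader might infer that 750 patients also lack 90% power. At SD 10 with r = 0.7 the pooled trial reaches 78-93% for 2.25 joints and at least 95% for three.

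**Conclusion.** The point holds, chiefly for the regional claim. The SD grid is too narrow for the population the article describes, and 90% power at 250 patients per region is not supported. The part that needs no outside assumption is that, without baseline adjustment, 250 patients lose 90% power above an SD of 4.3 (2.25 joints) or 5.8 (three joints), and the plan's own SD of 5 already falls short for 30% versus 15% of 15. The size of the loss beyond that depends on an SD the documents do not give. At an assumed SD of 10, regional power is 20-47% unadjusted and 35-75% with a baseline correlation of 0.7. The pooled analysis may be adequate at SD 10 with adjustment, but is less secure at SD 13.

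**What to change.** In the sample size section:

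1. Replace the SD range with one that covers the eligible population, for example 5, 10 and 15.
2. State which SD and which difference (2.25 or 3 joints) the calculation uses.
3. Withdraw or restate the 90% claim per region.
4. Give power and the detectable difference for the pooled 750, using the baseline adjustment already planned and a stated baseline correlation.
5. Estimate SD and ICC once, blind to arm, from the baseline counts already collected, and report the resulting power.

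The cost is one recalculated table and one blinded descriptive check. No extra patients and no change to the analysis model are needed. The drawback is a less favourable stated power, particularly for the regional comparisons.

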#### Statistical analyses

All data will be entered into a customized Access database (Microsoft, Redmond, Wash, USA). Analyses will be performed using Stata, version 12. All data will be analyzed by intention to treat. The tests were two-sided, with a type I error set at α = 0.05 (except for multiple comparisons when appropriate). Baseline characteristics (GPs and their patients) will be presented as the mean ± standard deviation (SD) or the median (interquartile range) for each randomization group for continuous data and as the number of patients and associated percentages for categorical parameters. Hierarchical linear regression models (mixed models) with levels for practice, individuals within practices, and repeated measurements per individual have been used to estimate effects of the intervention on number of joints smoked per month post-baseline time points. These models (intercept and slope as random effects) included an interaction between randomization group and time point, and adjusted for number of joints smoked per month at baseline, age of first consumption, gender, CAST at baseline, socioeconomic status, and GP’s characteristics. Intraclass correlation coefficients are presented by arm. The secondary analyses will compare changes on between groups with random effects models: method of consumption, supply method, perception of the effects on health, professional life, social life, and driving under the influence of alcohol will be also compared. This data will be collected through a self-administered questionnaire that the patient will complete and leave at the GP’s surgery. To assess the problem caused by missing data (GP and patients), estimation methods developed by Verbeke and Molenberg are proposed.

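### The 250-patient calculation is repeated in three regions to show regional variation, but the stated objective and model contain no regional question, and the design is not sized to compare regions

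*Protocol article*

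**What the plan says.** In the Protocol article, Sample size estimation sizes one two-group comparison "for 90% power and 5% two-sided type 1 error", with five patients per GP, losses of 10% of GPs and 20% of patients, and "intra-cluster correlation considered between 0.05 to 0.20". The result is 250 patients from 50 GPs. The text goes on: "This design is respected in each region for an analysis stratified by region and thus highlights a variation per region". The Abstract agrees: "This plan is replicated for the three areas, and therefore a total of 750 patients are expected".

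Other sections describe a trial with one question:

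- The end of the Background gives one main objective, the effect at 12 months. No objective, main or secondary, concerns a region.
- Randomization is stratified by region, because consumption and sociodemographic factors may differ there.
- Statistical analyses describes one hierarchical model with levels for practice, patient and repeated measurement, a group-by-time interaction and a list of covariates. Region is not in the list, and there is no group-by-region term.
- Tests are two-sided, "with a type I error set at α = 0.05 (except for multiple comparisons when appropriate"). This is the only statement on multiplicity.

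**The concern.** Repeating the design adds 500 patients and 100 GPs, and the only reason given is regional. Yet the stated model has no term that would deliver a regional result, and it omits the factor used to stratify randomization.

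Two things are at stake. First, the status of the pooled and regional results is not fixed, and an adjustment made only when appropriate leaves the choice open until the data are seen. Second, a reader is led to expect that the trial can show how the effect varies by region. Regions will differ by chance: with the same true effect everywhere and 90% power in each, at least one of three regional tests is non-significant with probability 1 − 0.9³ = 27%. Without a stated hierarchy, that could be reported as regional variation.

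**Working it through.** **Inputs from the article.** Two-sided alpha 5%; power 90%; 250 patients per region, 125 per arm; five per GP; ICC 0.05 to 0.20 (0.2 in the Abstract); SD 1.5, 2, 3, 4 or 5. For the effect, "we considered that cannabis users consumed an average of 15 joints per month" and reductions of 30% against 15% give 4.5 − 2.25 = 2.25 joints. The Methods section rounds the two reductions to five and two joints, a difference of three.

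**Assumptions.** The article does not say which SD, difference or ICC gives 250. I take retention as 0.9 × 0.8 = 0.72, so 125 × 0.72 = 90 patients analysed per arm per region, with four per GP after patient loss. The design effect is 1 + 3 × ICC. Normal approximations are used throughout.

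**The plan's figure.** 250 can be approached but not uniquely:

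- 2.25 joints, SD 4, ICC 0.10: 67 per arm, 2 × 67 × 1.3 / 0.72 = 242.
- 3 joints, SD 5, ICC 0.2: 59 per arm, 2 × 59 × 1.6 / 0.72 = 263.
- 2 joints, SD 3, ICC 0.2, with five per GP (design effect 1.8): 48 per arm, 2 × 48 × 1.8 / 0.72 = 240.

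So I first use the plan's own 90% per region, which needs no SD. It implies an expected z of 1.960 + 1.282 = 3.242 in each region.

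**Reading A: the group effect within each region.**

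- At 5% unadjusted, power is 90% per region.
- At 0.05/3 the critical value is 2.394, and power is Φ(3.242 − 2.394) = 80%. Keeping 90% needs ((2.394 + 1.282)/3.242)² = 1.286 times the patients, about 322 per region.
- If each region were tested at 5% and any success counted, the false-positive risk would be 1 − 0.95³ = 14.3%.

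**Reading B: differences between regions.** The contrast of two regional effects has √2 times the regional standard error.

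- Difference as large as the whole effect: z = 3.242/√2 = 2.292, power Φ(2.292 − 1.960) = 63%.
- Half of that: z = 1.146, power Φ(1.146 − 1.960) = 21%.
- One of three regions with no effect, 2-df test: noncentrality 3.242² × (1/9 + 1/9 + 4/9) = 7.00, critical value 5.99, power 66%.

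**Sensitivity to the unstated SD.** The regional standard error is SD × √(2 × (1 + 3 × ICC)/90). The 2-df column again has one region with no effect.

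| Joints | SD | ICC | Power per region at 5% | 2-df power |
|---|---|---|---|---|
| 2.25 | 5 | 0.20 | 66.5% | 40% |
| 2.25 | 4 | 0.20 | 85% | 58% |
| 3 | 5 | 0.20 | 89% | 64% |
| 2.25 | 3 | 0.20 | 98% | 84% |
| 2.25 | 3 | 0.05 | 99.7% | 94% |

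In this table the between-region test passes 80% only where power per region is far above the planned 90%.

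**Pooled test on 750.** At 90% per region, z = 3.242 × √3 = 5.615 and power exceeds 99.9%. The least favourable case for 2.25 to 3 joints, SD 3 to 5 and ICC 0.05 to 0.20 is 2.25 joints, SD 5, ICC 0.2. There the standard error is 5 × √(2 × 1.6/270) = 0.544 and power is Φ(2.25/0.544 − 1.960) = 98.5%. With a design effect of 1.8 (five per GP) it is 97.4%.

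**The case against.** The strongest reply is that the article already describes a pooled trial. It has one objective, one model and stratified randomization, and a region-stratified analysis ordinarily means a combined one with region as a stratum. On that reading alpha is 5% and power is ample. This stands as the likelier intention, and it rules out two stronger inferences that a reader might draw:

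- *That the trial carries a 14.3% false-positive risk.* No section announces three primary tests or counts success in any region. The figure is conditional on a rule that the article does not state.
- *That the regional tests are underpowered.* At the stated 90% and 5% they are not. The 66.5% per region and the 40% for heterogeneity belong to one corner of the grid (smaller difference, largest SD, largest ICC). Whether 250 suffices there is a separate sample-size question.

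A second reply concerns wording. The same section uses the word variation for the between-group difference ("a relative variation in the reduction in consumption of the amount of joints of 50% between the two groups (30% vs. 15"%), so the disputed phrase may mean only the effect within each region. That is possible, and it would remove the heterogeneity claim. It would leave three regional effects with no stated status and only an open multiplicity clause.

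A third reply is that a condensed article leaves the alpha rule to an analysis plan. That is fair for the rule itself. It does not cover a sample size justified by an analysis that the article's own model does not contain.

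**Conclusion.** The point holds as an inconsistency within the article. The size is tripled for a regional purpose that neither the objective nor the listed model serves, the stratification factor is missing from that model, and the pooled contrast is not named as the confirmatory test.

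The claim to show regional variation is secure on neither reading. For within-region effects, 90% falls to 80% once alpha is shared among three tests. For differences between regions, power is 63% to 66% for differences as large as the whole effect, and 21% for a two-region difference of half of it. These figures rest on the plan's own 90% per region, equal region sizes and normal approximations. With the SD unfixed, the 2-df power at 2.25 joints runs from about 40% (SD 5, ICC 0.2) to 94% (SD 3, ICC 0.05). The pooled question is not in danger: its power is about 97% or more for 2.25 to 3 joints, SD 3 to 5 and ICC 0.05 to 0.20.

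**What to change.** Before the 12-month data are analysed, state that the single primary test, two-sided at 5%, is the group difference at 12 months in all 750 patients, and add region to the hierarchical model. Make the region-specific effects and the group-by-region test secondary, reported as estimates with 95% confidence intervals and not as separate claims of efficacy. In Sample size estimation, delete the claim to show a variation per region, or say which variation is meant and give its actual power with the SD, ICC and difference assumed.

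This takes a few sentences and no extra patients. The sponsor gives up stand-alone regional efficacy claims. To keep them at 90% power with alpha divided by three would take about 322 patients per region, 966 in total.
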